### Sample size calculation

A remission in 65% and 40% of cases is assumed under the DS-CBT and DEP respectively. To detect a statistically significant difference with a power (1-β) of 90% (2-sided t-test, α = 0.05) 83 patients in each treatment group are required. Assuming a loss to follow-up of 20%, 104 patients in each arm of the trial are needed.

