### Within-trial economic evaluation

The objective of the economic evaluation, which is conducted alongside the trial, is to estimate the cost-effectiveness of the DS-CBT in terms of costs per quality adjusted year (QALY) from the perspective of the German statutory health insurance and from the societal perspective. To this end an incremental cost-effectiveness ratio (ICER) will be calculated, i.e. the ratio of the difference in costs between DS-CBT and DEP groups divided by the difference in QALYs gained in each group. Under statutory health insurance perspective on cost, ICER will be calculated using health sector costs only. Adopting the societal perspective, also patient costs and societal productivity costs will be added to the calculation of the ICER.

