### Estimating effects of intervention in terms of QALYs

For the purposes of economic analysis, measures comparable across various interventions as well as across different disease areas are preferred. Most popular outcome measure for this purpose are the quality adjusted life-years (QALYs), which explicitly combine length and quality of life in a single measure, weighting survival (a set of health states) by utility scores. Utility weights reflect preferences for a particular health state and are measured on a scale from 0 to 1, where 0 and 1 represent death and full health, respectively [25]. Although the trial does not include a utility measurement as part of its protocol, it does include the SF-36 and the EQ-5D questionnaires measuring health related quality of life. Standardized algorithms exist to translate EQ-5D and SF-36 scores into utility weights suitable for calculation of QALYs [26-28].

More than 15 value sets are available for scoring the EQ-5D, based on rating scale and time trade-off (TTO) valuation derived from general population surveys in various countries (including the United Kingdom, Germany, and the United States) [28]. In this study the scoring function derived from a survey of the general population in Germany will be used to calculate utility weights from EQ-5D responses [29].

Brazier and colleagues reported work on deriving a reduced health status index from the SF-36 that they termed the SF-6D [30] and more recently, they have published an algorithm that allows the estimation of utility weights for all states of the SF-6D index [31]. Following this published algorithm, SF-36 scores observed in the trial will be converted to utility weights. Since the values underlying this algorithm were obtained in the United Kingdom, utilities derived from SF-36 scores will be only used to perform a sensitivity analysis.

The SF-36 and EQ-5D will be administered at baseline, immediately after the intervention, at 6 months and at 12 months after the intervention (see Table 1). Hence, a maximum of four possible observations for SF-36 and EQ-5D scores and derived utility weights will be available for each patient enrolled in the trial. QALYs will be calculated assuming linear interpolation between measurement points and calculating the area under the curve to give a number of QALY gained per patient over the trial period [25].

**Table 1 T1:** Endpoints, measurement instruments and time of data collection

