### Statistical analysis of costs and effects

Mean total costs, health sector costs, patient costs and productivity costs as well as corresponding cost differences between the DS-CBT group and DEP group will be calculated. Sampling uncertainty (95% confidence intervals) will be estimated using bootstrap procedure because cost data are non-normally distributed.

Effect in terms of QALYs will be analysed using linear regression on type of intervention and - if necessary - on baseline utility score, which has been shown to be important for the unbiased assessment of mean QALY differences between treatment groups [32].

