### Determining cost-effectiveness

If a significant impact of DS CBT on both effects and costs is demonstrated, ICER will be estimated in terms of costs per QALY gained. ICER will be estimated for the total cost (health sector costs plus patient costs plus societal productivity costs) and for the health sector costs only (statutory health insurance perspective). The non-parametric bootstrap method will be employed to generate confidence intervals around the ICER estimates derived from the study sample [38,39]. Uncertainty surrounding the ICER will also be presented on the cost-effectiveness plane [40,41] and as the cost-effectiveness acceptability curve [42,43].

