### Sensitivity analyses

Besides statistical uncertainty (sampling variation) with regard to costs and effects, every economic evaluation may contain some degree of data imprecision (e.g. resource costs/prices) and methodological controversy (e.g. derivation of utility weights, discount rate), which should be accounted for. To handle this type of uncertainty, sensitivity analysis is usually employed [25,44]. In the sensitivity analysis (uncertain) parameter(s) of the base-case analysis are varied to determine if changes in these parameters influence the results. Univariate sensitivity analyses will be performed by varying health service unit costs and utility weights (see Table 2). To appreciate the potential influence of missing responses and of the imputation method chosen, complete case analysis will be performed. We will report both the revised point estimates and revised confidence intervals for costs, effectiveness, and cost-effectiveness that result from the sensitivity analyses.

**Table 2 T2:** Summary of planed sensitivity analyses

Parameter/methodological assumption	Base-case	Sensitivity analysis
Utility weights for QALYs	derived from the EQ-5D	derived from the SF-36

Unit costs/prices of resource use	data from published sources and official statistics for Germany	varied within a plausible range

Missing data	multiple imputation	complete case analysis

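### The QALY regression adjusts for baseline utility only 'if necessary', with no criterion, although the plan itself calls that covariate important; the adjustment should be fixed in advance

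*Protocol article*

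**What the plan says.** Under *Statistical analysis of costs and effects*, the article plans to analyse QALYs by "linear regression on type of intervention and - if necessary - on baseline utility score". The sentence goes on to describe the baseline score as something "which has been shown to be important for the unbiased assessment of mean QALY differences between treatment groups".

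Three other places bear on this:

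- *Estimating effects of intervention in terms of QALYs* sets the measurement times: "The SF-36 and EQ-5D will be administered at baseline, immediately after the intervention, at 6 months and at 12 months after the intervention". It also sets the outcome: "QALYs will be calculated assuming linear interpolation between measurement points and calculating the area under the curve".
- *Determining cost-effectiveness* makes the main economic result conditional: "If a significant impact of DS CBT on both effects and costs is demonstrated, ICER will be estimated in terms of costs per QALY gained".
- *Sensitivity analyses* says: "Univariate sensitivity analyses will be performed by varying health service unit costs and utility weights". Table 2 adds complete case analysis for missing data. It lists no comparison of adjusted and unadjusted QALY differences.

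No section says what would make adjustment necessary, who decides, or when.

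**The concern.** One sentence gives the reason for the covariate and then makes it optional. With no stated criterion, the decision can be taken after outcome data have been seen. Availability does not explain the condition, because EQ-5D and SF-36 are both scheduled at baseline.

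Three things are at stake:

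1. **Precision.** Utilities measured repeatedly in the same patient are usually correlated. Leaving out the baseline value then leaves explainable variance in the QALY difference.
2. **Chance imbalance.** A baseline difference that arises by chance carries over into the unadjusted QALY difference, whether or not anyone would call it notable.
3. **Discretion.** Two QALY differences will be available, and the plan does not say which one counts. A significant effect is one of the two conditions for estimating the ICER, so the choice can affect both the size of the denominator and whether an ICER appears.

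**Working it through.** **The plan's own figure.** The article states no figure for the QALY regression. Its sample size rests on remission: "A remission in 65% and 40% of cases is assumed under the DS-CBT and DEP respectively". With two-sided α = 0.05 and 90% power, the pooled two-proportion formula gives

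n = [1.960·√(2·0.525·0.475) + 1.282·√(0.65·0.35 + 0.40·0.60)]² / 0.25² = 81.7, so 82 per arm.

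The stated 83 agrees within rounding of methods, and 83/(1 − 0.20) = 103.75 gives 104. These figures are sound. They enter below only as the number of patients per arm.

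**Inputs.** From the article: 104 per arm, equal allocation, linear regression. Assumed, because the article gives no value: a correlation r between baseline utility and QALYs of 0.3, 0.5 or 0.7; normal data; and, for power only, a true effect of 0.4 SD.

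**How baseline reaches the outcome.** With trapezoids, the baseline value carries half of the first two-week interval, that is 1 of about 52 weeks or roughly 2% of the area. The direct contribution is small. The shift comes mainly through the within-patient correlation that r represents.

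**Chance imbalance.** The standard error of the baseline difference is √(2/104) = 0.139 SD. A one-standard-error imbalance moves the unadjusted QALY difference by r × 0.139 SD.

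**Precision.** Adjusting multiplies the variance of the QALY difference by 1 − r². Simulation agrees: at r = 0.7 the ratio of SDs is 0.0996/0.1398 = 0.712, and 0.712² = 0.51.

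**Error rate and power.** Trials of 104 per arm were simulated, 6,000 per setting under no effect and 3,000 per setting for power. Three policies were compared: always adjust; take whichever model gives the smaller p-value; adjust only if a baseline t-test gives p < 0.05.

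| | r = 0.3 | r = 0.5 | r = 0.7 |
|---|---|---|---|
| Shift from a 1-SE imbalance (QALY SD) | 0.042 | 0.069 | 0.097 |
| Variance cut by always adjusting (r²) | 9% | 25% | 49% |
| Type I error, always adjust | 4.9% | 4.7% | 5.0% |
| Type I error, smaller p-value chosen | 6.3% | 6.9% | 8.5% |
| Type I error, baseline-test trigger | 4.7% | 4.0% | 3.6% |
| Power, baseline-test trigger | 83.0% | 83.8% | 84.1% |
| Power, always adjust | 85.7% | 91.3% | 98.1% |

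The simulation error on the type I figures is about 0.3 to 0.4 percentage points (for example √(0.05·0.95/6000) = 0.003). With 83 per arm, the figures for the smaller p-value are 5.9%, 7.7% and 8.6%, so the conclusion does not depend on dropout.

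**The case against.** The best reply is that this is a narrow wording point in a condensed article. QALYs are not the primary endpoint, the sample size is untouched, the covariate is named with a source, and an analysis plan not shown may define the condition. The scope argument stands and limits the weight of the point. The argument from an unseen plan does not settle it. The article is not silent on covariates: it states a conditional rule at odds with its own reason. A definition that depended on observed baseline data would still do worse than always adjusting.

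A reader might also infer four stronger things, which the document does not support:

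- **That the unadjusted difference is biased.** Patients are randomised, so it is unbiased on average. The article calls the covariate important, not indispensable. The shift in question is conditional on a chance imbalance.
- **That the ICER is defined on a raw difference.** *Within-trial economic evaluation* speaks of a cost difference "divided by the difference in QALYs gained in each group". That is the general definition of an ICER and does not say unadjusted. The article only leaves unsaid which estimate enters.
- **That adjustment hangs on a baseline significance test.** No such test is mentioned. If there were one, the procedure would be conservative, and the cost would be power rather than false positives.
- **That confidence intervals would generally cover too little.** At an assumed correlation of 0.6, the unadjusted interval covers less than 95% only for imbalances beyond about 1.07 standard errors. It covers more than 95% below that.

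The inflation to 6–8.5% also needs an analyst who picks the smaller p-value. The plan permits that, but nothing suggests it is intended.

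**Conclusion.** The point holds as a defect of specification. The condition on baseline utility is undefined and conflicts with the reason given beside it, and nothing in the article requires it. Always adjusting would be a gain without a price: under the assumed correlations it lowers the variance of the QALY difference by 9% to 49% and keeps type I error at about 5%. The upper bound on harm from discretion is a type I error of about 6–8.5%. All these sizes are illustrative, because they rest on assumed correlations, normal data and, for power, an assumed effect of 0.4 SD. The change should be made, but it does not touch the primary endpoint or the sample size.

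**What to change.** - Delete the words 'if necessary'. Always regress QALYs on arm and the matching baseline utility: the EQ-5D baseline value for the base case and the SF-6D baseline value (from the SF-36) for the sensitivity analysis.
- Fit this model in every imputed data set and every bootstrap replicate.
- State that the adjusted difference is the denominator of the ICER and is the effect used on the cost-effectiveness plane and in the acceptability curve.
- The unadjusted difference may be added to Table 2 as a sensitivity analysis.

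The cost is two words removed and a sentence or two added. Both questionnaires are already scheduled at baseline, and the number of patients does not change.

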### Imputation of missing information on costs and effects

Data will be analysed according to the intention to treat principle. A multiple imputation approach based on propensity scoring will be used to account for missing information with regard to effects and costs. Baseline variables (e.g. age, gender, cost at baseline, etc.) will be entered into a logistic regression to predict the chance of a missing value [33,34]. Available data will be arranged into quintiles based on this predicted probability (propensity score) and a replacement value for missing data will be selected at random from the available data points within the same quintile. By choosing a value at random within the same quintile the principle of multiple imputations could be employed, whereby each missing value is replaced by m > 1 simulated values [35-37]. Each of *m *resulting data sets will be analysed as described above and combined to produce a single result that takes uncertainty in the imputation process into account.

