### Measurement of resource use

Resource use and costs directly associated with DS-CBT and DEP (e.g. staff time) will be derived from the therapy protocols. Information on the utilisation of other healthcare services will be obtained from trial participants by means of a cost questionnaire, which was developed for the study and incorporated into the case report files of the trial. The questionnaire is administered before the intervention (baseline), at 6, and 12 months of the trial and refers to the previous 6 months (see Table 1). The cost form includes structured no/yes questions on the utilisation of different medical services under the following categories: primary care visits, visits to emergency departments, visits to specialists, hospital stays, medication, and other therapies/paramedical care. If patients indicate that they received specific medical care over the past 6 months, they are asked to specify the volume: e.g. number of contacts with healthcare providers, number and length of hospitalizations, types and dosage of obtained medications. In the cost questionnaire patients are also asked to indicate whether health care services obtained by them were paid by the health insurance or self-paid, which makes an assessment of out-of-pocket expenses possible. Furthermore, the number of "days missed from work" will be registered with the cost questionnaire.

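### As written, the base-case imputation of costs and QALYs ignores treatment arm, so imputed values carry no treatment effect and differences in the imputed quantities shrink toward zero

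*Protocol article*

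**What the plan says.** The section on imputation of missing information on costs and effects sets out a specific procedure:

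- Missingness model: "Baseline variables (e.g. age, gender, cost at baseline, etc.) will be entered into a logistic regression to predict the chance of a missing value".
- Cells: quintiles of the predicted probability, formed over the available data.
- Donor rule: "a replacement value for missing data will be selected at random from the available data points within the same quintile".
- The draw is repeated to give several completed data sets, which are analysed and combined.

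The analysis section then estimates the effect of arm: "Effect in terms of QALYs will be analysed using linear regression on type of intervention", with baseline utility added if necessary. Mean costs are also compared between arms.

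Three other statements bear on the point. Loss is anticipated: "Assuming a loss to follow-up of 20%, 104 patients in each arm of the trial are needed". Intervention costs have their own source: "Resource use and costs directly associated with DS-CBT and DEP (e.g. staff time) will be derived from the therapy protocols". Table 2 makes multiple imputation the base case and complete case analysis the sensitivity analysis.

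**The concern.** An imputation procedure should condition on whatever the later analysis conditions on. Here the analysis estimates the effect of arm, but the imputation does not mention arm. If the donor pool is simply the quintile, a DS-CBT patient with a missing value may receive a control patient's value, and the reverse. The imputed part of each arm then has the same expected value, which dilutes the contrast.

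The missingness predictors are all baseline variables. A patient's own 2-week and 6-month utilities and 6-month costs, which would normally inform the 12-month values, play no part.

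This affects the base-case economic result. Under the section on determining cost-effectiveness, the ICER is estimated only after significant effects on both outcomes and costs, so a diluted difference also bears on whether the ICER is reported at all. In addition, the Background motivates the study by possible savings in other healthcare costs. Those savings come from the patient questionnaire, which is the part open to imputation.

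**Working it through.** **The plan's own figures.** "A remission in 65% and 40% of cases is assumed under the DS-CBT and DEP respectively"; "with a power (1-β) of 90% (2-sided t-test, α = 0.05) 83 patients in each treatment group are required". The arcsine formula gives 82.06, rounded up to 83, and power at 83 per arm is 90.4%. Allowing for loss, 83 / (1 − 0.20) = 103.75, or 104. The sample size therefore reproduces. The plan gives no figure for the effect of the imputation, nor an SD or expected difference for QALYs or costs.

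**Closed form.** Let δ be the true difference, m1 and m0 the missing fractions in DS-CBT and DEP, and w the DS-CBT share of donors. With donors drawn regardless of arm, every imputed value has expectation μ0 + wδ. Then:

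- DS-CBT mean = (1 − m1)(μ0 + δ) + m1(μ0 + wδ)
- DEP mean = (1 − m0)μ0 + m0(μ0 + wδ)
- Difference = δ × [1 − m1(1 − w) − m0·w]

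With m1 = m0 = 0.20 this is δ × 0.80. With 30% missing in one arm and 10% in the other (for DS-CBT 30%, w = 0.70 / 1.60 = 0.4375), it is 1 − 0.30 × 0.5625 − 0.10 × 0.4375 = 0.79.

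**Simulation.** 104 per arm, 5 imputations, 1000 runs per scenario, outcome missing at random given baseline covariates. Effect sizes (0.4 SD and 1 SD), covariate strengths and the missingness model are assumptions. Entries are estimated / true difference.

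| Missing | Donors pooled, arm not used | Arm in propensity model, donors pooled | Quintiles and donors within arm |
|---|---|---|---|
| about 11% | 0.87 | 0.91 | 1.00 |
| about 21.5% | 0.78–0.79 | 0.80 | 0.97–1.01 |
| about 31% | 0.70 | 0.71 | 1.00 |
| DS-CBT 30%, DEP 10% | 0.77 | 1.05 | 0.97 |
| DS-CBT 10%, DEP 30% | 0.79 | 0.77 | 1.03 |

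The pooled results match the closed form (1 − 0.215 = 0.785). Complete case estimates were unbiased in the same runs (0.97 to 1.02). At 21.5% missing, an assumed 0.4 SD effect and baseline adjustment, power was 68% with pooled donors and 85% within arm. Coverage of the 95% interval with pooled donors was 68–75% at a 1 SD effect, but about 94–95% at 0.4 SD. At the smaller effect the loss is therefore mainly of size and power.

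**QALYs when utilities are imputed per visit.** The area under the curve over 0, 2 weeks, 6 and 12 months gives weights of 0.5/2 = 0.25 at 2 weeks, (1 − 2/52)/2 = 0.48 at 6 months and 0.5/2 = 0.25 at 12 months, in total 0.98. Assuming a constant effect from week 2 and equal missingness by arm, shrinkage is:

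- 20% missing at 12 months only: 0.25 × 0.20 / 0.98 = 5%
- 10% at 6 months and 20% at 12 months: (0.48 × 0.10 + 0.25 × 0.20) / 0.98 = 10%
- 20% at all three visits: 20%

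If the whole QALY is imputed for 20% of patients, shrinkage is 20%.

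**Costs (purely illustrative amounts).** Only the questionnaire part is diluted.

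- Intervention +300, other costs −200, 20% missing throughout: the true net of +100 becomes 300 − 0.8 × 200 = +140. The cost difference grows.
- Intervention +300, other costs +700 spread evenly over two six-month periods, 20% missing at 12 months only: other costs shrink by 10%, so 1000 becomes 300 + 630 = 930. QALYs shrink by 5%. The ICER changes by a factor of 0.93 / 0.95 = 0.98, a fall of about 2%.

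**The case against.** The strongest reply is that the article never says donors are pooled. It is silent on arm, its list of predictors is open-ended, and running the imputation by arm is the kind of detail a condensed article may leave to a fuller document. This stands in part: pooling is the literal reading and not an explicit statement. But the donor rule is stated, the cell is the quintile, and no restriction by arm is given, so an analyst following the text would produce the bias. Reading arm into the open list does not rescue it. With arm only in the propensity model the ratio was 0.77, 0.80 or 1.05, depending on how missingness fell between arms.

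A second reply is that the complete case analysis is planned expressly to judge the imputation method. That is a real safeguard, and a gap between the two analyses could show the problem. It leaves the base case uncorrected.

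A reader might also infer more than the documents support:

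- *That QALY and total cost differences both shrink by the missing fraction.* For QALYs this needs whole-QALY imputation or equal loss at every follow-up visit. For costs it ignores that intervention costs come from the therapy protocols.
- *That the ICER necessarily moves against DS-CBT, by up to 1 / 0.8 = 1.25.* That factor needs a cost difference consisting only of intervention cost and a full 20% QALY shrinkage. The second cost illustration goes the other way.
- *That variances are understated and the cost–QALY correlation is broken.* These depend on whether a donor's costs and QALYs are drawn jointly and whether the donor pool is resampled, which the article does not fix. They are secondary.

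**Conclusion.** The point holds in this form: the stated base-case procedure does not condition on arm and leaves out observed follow-up values. Followed literally, it pulls differences in the imputed quantities toward zero. At the plan's 20% loss the pull is about 20% for an outcome imputed as a whole or missing equally at every follow-up visit. For QALYs imputed per visit it is about 5% to 20%, assuming a constant effect from week 2. Questionnaire-based costs are diluted and intervention costs are not, so the direction of the net cost difference and the ICER cannot be stated in advance.

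The shrinkage factor follows algebraically from drawing donors without regard to arm. The power and coverage figures rest on assumed effect sizes. The point concerns the economic evaluation; the imputation paragraph covers costs and effects there and does not address the trial's primary endpoint, reduction of depression at 12 months.

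**What to change.** State in the imputation section that the propensity model, the quintiles and the donors are formed separately within each arm. In the simulations this alone removed the systematic shrinkage. Adding arm to the logistic model while leaving donors pooled is not a substitute.

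Alternatively, use multiple imputation run by arm that also includes the observed 2-week and 6-month utilities and the 6-month costs. This deals with both parts of the point.

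In either case, say whether the imputed unit is the visit-level utility and cost or the whole-trial total, since this determines how much is at stake. Keep the complete case analysis as planned.

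The cost is a rewording of one paragraph, somewhat smaller donor cells (at 20% loss, 83 observed patients per arm over five quintiles is about 17 donors per cell) and a little more programming. No extra data are needed.
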